#### Strategies to improve adherence to intervention

Adherence to the intervention will be monitored based on the data received from the devices.

#### End of trial

At end of trial, participants from both groups visit the endocrinology clinic again. The participants are encouraged to answer various questionnaires and a laboratory technician/nurse will take a venous blood sample. The flow of the trial design is illustrated in Fig. 1.

**Fig. 1 Fig1:**
[figure not shown]
The 3-month flow of the trial

### Outcome measures

#### Primary endpoint

Change from baseline in CGM time in range (3.9–10.0 mmol/L) 3 months after randomization.

#### Secondary endpoints

Change from baseline in HbA1c 3 months after randomizationChange from baseline in total daily dose 3 months after randomizationChange from baseline in CGM time in time below range (≤3.9 mmol/L) 3 months after randomizationChange from baseline in CGM time in time above range (>10.0 mmol/L) 3 months after randomization

#### Exploratory endpoints

The exploratory endpoints are based on questionnaires and monitoring data, and include the following:5)Change from baseline in CGM endpoints 3 months after randomization: number of days worn, percentage of time active, mean glucose, glycemic variability, time in hyperglycemia (>13.9 mmol/L), time in hypoglycemia (<3.0 mmol/L), episodes (hypoglycemia and hyperglycemia) 15 min and area under the curve.6)Use of the telemonitoring equipment: The frequency of use of the telemonitoring equipment during the trial is assessed directly from the delivered devices.7)Telemonitoring usability: Data is collected via the Telemedicine Usability Questionnaire. The telemedicine group will answer the questionnaire at the 3-month assessment.8)Diabetes-related quality of life: Between group differences measured by the DIDP questionnaire at baseline and at the 3-month assessment.9)Quality of Life: Between group differences measured by the SF-12 questionnaire at baseline and at the 3-month assessment.10)Adherence to insulin dosing and timing. Any differences in the use of insulin between the two groups are examined based on data from the insulin pens.11)Number of hypoglycemic events 3 months after randomization.

In addition, qualitative interviews will be conducted with selected participants in order to gain deeper insight into the participants’ experience of telemonitoring.

Hospital staff will make appointments with the participants for the final visit, during which the final data will be collected. Should a participant not show up for the appointment, hospital staff will contact the participant by telephone to schedule a new appointment. Participation in the final visit is considered to be completion of trial regardless of the degree of use of technologies. The trial ends after the last participant’s final visit.

#### Data management

Data will be archived both manually and on a computer in RedCap. Signed statements of informed consent as well as completed questionnaires are stored and kept locked. Questionnaire replies and other relevant patient data are entered and stored in RedCap. There will be access protection on both computer and used storage media, which is known only by the investigator, subinvestigator, and relevant members of the project team. Review and manipulation of third party data will only take place by agreement between the subinvestigator and the primary investigator. Data will be stored for the period notified to the Danish Data Protection Agency. In the event of a request for renewal, the trial will be reassessed for the purpose of permission. Data cleaning is performed during the entire conduction of the trial. Checks include cross-validation of dates, search for duplicates, and source data verification and are fired on collected data. Correction of source data follows ICH guidelines for good clinical practice.

#### Confidentiality

Information about the participants will be obtained during trial inclusion. This information includes health status, medication, and comorbidities. This information is collected for two reasons. First, the information is obtained to ensure the suitability of the subjects in relation to inclusion in the study. Second, the information along with demographic data must be used for later analysis in an anonymized form. No information will be obtained until the participant has given her/his consent. This consent gives the primary investigator, subinvestigators, and delegated project team members direct access to obtain information in the participants’ journal, including the electronic journal. The obtained information will include the participants’ health conditions, which is necessary in order to complete the trial and for the purpose of control, including self-regulation, quality control, and monitoring. Only staff affiliated with Steno Diabetes Center will have access to the information in the patients’ journal. Other parties in the ADAPT consortium will not have access to any personally identifiable data.

#### Plans for collection, laboratory evaluation, and storage of biological specimens

As described, a blood sample is drawn at the beginning and at the end of the trial for all included subjects. This is initially done for analysis of the following: HbA1c, lipids, c-peptide, and insulin. Approx. 60 ml will be drawn per sample. All samples will be analyzed immediately after extraction at Aalborg University Hospital, after which the samples will be destroyed.

A research biobank is set up to collect material for later analysis of parameters, which were not possible to predict before the start of the trial. This specifically includes cardiovascular risk and bone disease associated with glucose variation. These factors include:P1NPCTXSclerostinGlucagonPlasma-ionized calciumPlasma albumin-adjusted calcium

All blood samples will be taken and handled by lab technicians/nurses at SDCN or SDCS during the initial and final visit. All biological material is destroyed at the end of the project when all analyses related to the specific research project have been completed.

### Statistical analysis

Sample size calculation is based on the following formula:$$n=\frac{2{\sigma_d}^2}{\tau^2}{\left({z}_{a/2}+{z}_{\beta}\right)}^2$$

*τ* is the minimum detectable difference in mean and *σ*_*d*_ is the standard deviation of the difference. Based on an assumed difference in reduction of CGM time in the range of 80 min (*τ* =  − 80), a standard deviation of the difference of 220 min (*σ*_*d*_ = 220) [34], a significance level of 0.05 and a power of 0.9, the number of participants is 320. With an estimated dropout rate of 25%, 400 participants must be included. The large dropout rate is primarily expected in the usual care group. To minimize loss to follow-up, the trial staff will provide the participant in the usual care group with a printout of their data at study completion and offer a consultation regarding the data.

A variety of statistical methods will be applied to investigate the objectives of the trial after end of trial. No analysis is planned during the data collection period. All statistical methods will be applied on the Full Analysis Set that includes all randomized participants. Imputation of missing data is described below.

Change in CGM metrics and total daily insulin dose will be calculated as the difference between mean of the metric, e.g. time in range, or total daily insulin dose the 2 weeks before end of trial and the 2 weeks after randomization. Using data from all patients, the primary endpoint will be investigated with the following primary analysis. The primary analysis is performed with a statistical model that includes multiple imputation, where patients without CGM at scheduled visits get their CGM time in range imputed. An analysis of variance model with the region as a factor and CGM time in range at baseline as a covariate is used to estimate the effect of telemonitoring on CGM time in range. Sensitivity analysis with similar configurations will be applied to subgroups.

The secondary endpoints will be investigated using statistics, models, and algorithms that include differential equations in compartment modeling, as well as algorithms in Machine Learning.

All participants included in the trial will be included in the statistical analyzes. The statistical significance level of 5% is used in the trial (*p* < 0.05). Participation in the final visit is considered to be completion of trial regardless of the degree of use of technologies. The trial ends after the last participant's final visit.

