**Methods:**

The trial is an open-label randomized controlled trial with a trial period of 3 months conducted in two sites in Denmark. Patients with T2D on insulin therapy will be randomized (1:1) to a telemonitoring group (intervention) or a usual care group (control). The telemonitoring group will use a continuous glucose monitor (CGM), an insulin pen, an activity tracker, and smartphone applications throughout the trial. Hospital staff will monitor the telemonitoring group and contact the subjects by telephone repeatedly throughout the trial period. The usual care group will use a blinded CGM the first and last 20 days of the trial and will use a blinded insulin pen for the entire period.

The primary endpoint will be changed from baseline in CGM time in range (3.9–10.0 mmol/L) 3 months after randomization. Secondary endpoints include change from baseline in glycated hemoglobin (HbA1c), total daily dose, time above range, and time below range 3 months after randomization. Exploratory endpoints include health-related quality of life, diabetes-related quality of life, etc.

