### Eligibility criteria

We aim to include 400 participants. The participants will all be patients with T2D who are already treated with insulin. The participants will receive an insulin pen from Novo Nordisk A/S, which only works with Novo Nordisk products. Therefore, participants who are not treated with Novo Nordisk insulin will be shifted to Novo Nordisk basal insulin (Tresiba®) by trial initiation. If the participants should have any problems, concerns, or questions related to the shift in insulin, a telephone hotline with trained staff will be available for the participants 24/7.

Participants will be included based on the following criteria: Women and men ≥ 18 years, T2D diagnosis for ≥ 12 months, residence in Region North Denmark or Region Zealand, in treatment with insulin, being able to use a smartphone along with the other devices to be used in the trial, and able to understand and read Danish. Diagnosis of T2D was defined as either (1) glycated hemoglobin A1c ≥ 48 mmol/mol; (2) venous plasma glucose ≥11.1 mmol/l incl symptoms of polyurea, polydipsia, unexplained weight loss, or recurrent infections; or (3) venous plasma glucose ≥ 7.0 mmol/l or a 2-h plasma glucose ≥ 11.1 mmol/l after an oral glucose tolerance test. Participants will be excluded based on the following criteria: pregnancy or breastfeeding, major surgery planned during the trial period, participation in other trials, and terms that, in the opinion of the investigator or subinvestigators, render the participant unfit to conduct the trial, including lack of understanding of the trial or lack of physical or cognitive ability to participate.

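### The dropout allowance is miscalculated: 320 completers at 25% dropout needs 427 participants, and 400 leaves 300 completers, with about 88% power at best by the plan's own formula

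*Protocol article*

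**What the plan says.** The Statistical analysis section of the Protocol article gives a two-sample formula for comparing means. Its inputs are a "difference in reduction of CGM time in the range of 80 min" and "a standard deviation of the difference of 220 min". The result is stated as "a significance level of 0.05 and a power of 0.9, the number of participants is 320".

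The dropout allowance follows: "With an estimated dropout rate of 25%, 400 participants must be included". The next sentence says where the loss is expected: "The large dropout rate is primarily expected in the usual care group".

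The Eligibility criteria section carries the same total forward as the recruitment target: "We aim to include 400 participants". The Abstract (Methods) gives the allocation: participants "will be randomized (1:1) to a telemonitoring group (intervention) or a usual care group (control").

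**The concern.** Four printed figures belong together: 320 needed, 25% dropout, 400 included, 90% power. They cannot all be true, because a quarter of 400 is 100 and the 300 who remain are fewer than 320. The total of 400 fits the other figures only if dropout is 20%, or if 25% was added to 320 as a mark-up and then described as a dropout rate.

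This total sets the size of the trial. Ethics reviewers and later readers use the sample size statement to judge whether a null result on the primary endpoint is informative. As printed, it overstates either the dropout the trial can absorb or the power it has. The sentence on usual care adds to the problem. The formula assumes equal arms, and for a fixed number of completers equal arms give the most power. The plan itself expects an imbalance.

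**Working it through.** **Inputs** (Protocol article, Statistical analysis, except where noted)

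- Difference τ = 80 min; SD σ = 220 min
- Two-sided α = 0.05 (the formula uses z at α/2), z = 1.960
- Power 0.90, z = 1.2816
- Allocation 1:1 (Abstract, Methods)
- Dropout 25%, mainly in usual care, with no split given

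**Step 1: reproduce the size before dropout.**

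n per arm = 2σ²/τ² × (z_α/2 + z_β)² = 2 × 220²/80² × (1.960 + 1.2816)² = 158.9

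That is 159 per arm and 318 in total. The printed 320 (160 per arm) agrees after rounding up. A one-sided test would need only 260 in total, so the two-sided reading is the right one. The 320 is therefore sound, and it is the number needed before any loss.

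**Step 2: allow for dropout.** To keep N completers when a fraction d is lost, randomize N/(1 − d).

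- 320/(1 − 0.25) = 426.7, so 427, or 428 with equal arms (214 each)
- Starting from 318: 318/0.75 = 424
- Printed total: 320 × 1.25 = 400
- Dropout that 400 does tolerate: 1 − 320/400 = 20%
- Completers left from 400 at 25%: 400 × 0.75 = 300

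The shortfall is 427 − 400 = 27 participants, about 6% of 427. From the unrounded 318 it is 24. Rounding does not account for it.

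**Step 3: power with the completers that remain.** Power = Φ(τ/SE − 1.960), with SE = 220 × √(1/n₁ + 1/n₂).

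| Telemonitoring / usual care completers | Total | SE (min) | Power |
|---|---|---|---|
| 160 / 160 (as planned) | 320 | 24.6 | 90.2% |
| 150 / 150 (25% lost in each arm) | 300 | 25.4 | 88.3% |
| 180 / 120 (10% and 40% lost) | 300 | 25.9 | 87.0% |
| 190 / 110 (5% and 45% lost) | 300 | 26.4 | 85.9% |
| 200 / 100 (all loss in usual care) | 300 | 26.9 | 84.4% |

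A noncentral t calculation gives almost the same values: 88.1% at 150/150 and 84.1% at 200/100. The three unequal splits are assumptions. Only their direction comes from the plan, and the last is the extreme case.

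**The case against.** **The loss is small.** With equal dropout the gap is 1.7 points (88.3% against 90%). The larger gaps depend on assumed splits, and the 84.4% figure requires half of usual care to leave and nobody in the other arm. This is fair, and it limits the size of the claim. It does not reconcile the figures, and the equal split is the best case for power, which the plan says it does not expect.

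**The planned analysis is not the planning formula.** The primary model adjusts for region and for baseline time in range, so its power could exceed the unadjusted figures. Suppose that 220 min is the SD of the change and that variances are equal at baseline and follow-up. The adjusted variance is then (1 + ρ)/2 of the change-score variance, where ρ is the baseline to follow-up correlation. On those assumptions 90% power returns at 150/150 for ρ up to about 0.89, and at 200/100 for ρ up to about 0.68. For ρ from 0.5 to 0.8, power would be about 95% to 91% at 150/150 and about 93% to 88% at 200/100. This is the strongest point. It means that the actual analysis cannot be said to fall below 90%. But the article gives no ρ and the calculation claims no gain from adjustment, so the printed 90% has no support from that source.

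**All randomized participants are analysed, with multiple imputation.** Imputation keeps everyone in the analysis set but does not in itself restore the outcome information that dropouts take with them. By inflating the sample for dropout, the plan accepts this.

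**The consequence is only a sentence.** The error does not bias the estimate, affect type I error or leave the analysis unclear. That is true, and it is why the remedy is small. A stated design figure is still wrong.

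**Conclusion.** The concern holds: the figure is wrong as written. The 320 is correct. The 400 is not the number that 25% dropout requires, which is 427 (428 with equal arms). It is the right number for 20% dropout.

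On the plan's own unadjusted formula and inputs, 400 randomized with 25% lost gives 88.3% power if the loss is equal and as little as 84.4% if it all falls in usual care, against the 90% stated. That is about 2 to 6 points. The lower end of that loss follows from the printed figures alone, and the rest depends on a split that the plan does not give. The result assumes that dropouts contribute no outcome information and takes no credit for baseline adjustment, which could offset the loss by an amount the article does not allow anyone to calculate. The accurate statement is that the planning calculation does not support 90% power at 25% dropout.

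**What to change.** Keep 400 and correct the sentence in Statistical analysis in one of two ways, according to the dropout the investigators really expect.

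- **If 25% is the expectation:** state that 400 randomized participants leave 300 completers and about 88% power by the unadjusted formula, falling to about 84% if all dropout occurs in usual care.
- **If 20% is the expectation:** state that 400 participants allow for 20% dropout and retain 320 completers, and remove the 25%.

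Either version costs one sentence. No extra participants are needed, and neither the design nor the analysis changes. Under the first option the stated power becomes about 2 to 6 points less favourable. If the sponsor wants to count the gain from baseline adjustment, the assumed correlation should be stated with its source. The target in Eligibility criteria stays at 400 and needs no change.

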### The intervention

#### The telemonitoring group

The telemonitoring group will be provided with a continuous glucose monitor (CGM), a new smart pen from Novo Nordisk A/S, an activity tracker, and a smartphone (unless the participant prefers to use his/her own smartphone). The smart pen will be used for long-acting insulin for all participants. A second smart pen will be provided to those participants who are also on short-acting insulin. The participants will be trained to use the technologies provided at trial inclusion.

The telemonitoring group will use the distributed devices continuously to collect, log, and transfer tissue glucose levels, insulin administration, activity, and sleep at home for the entire trial duration. Laboratory technicians/nurses affiliated with the endocrinology clinics will perform the monitoring. The frequency of monitoring is tailored to the needs of each individual participant. The monitoring laboratory technicians/nurses will contact the participant by phone at least three times — at 1 week, 1 month, and 2 months after inclusion in the trial. Participants may be contacted on an ongoing basis if it is considered relevant by the monitoring lab technicians/nurses. The first phone call, after 1 week, is performed with an eye to ensuring that the participants have started the monitoring successfully and understand how to use the devices. During the calls after one month and 2 months after inclusion, the monitoring lab technicians/nurses will talk to the participants about their data from the past month. The ongoing calls are expected to have a more specific focus. Such calls will be performed if the lab technicians/nurses monitor data that they consider to be unusual. The frequency of such calls will thus rely on the individual assessment of the lab technicians/nurses, as they are not supported by any decision support algorithms. The monitoring lab technicians/nurses may give treatment advice during all calls and potentially change insulin doses based on the monitored data (after consulting a doctor). The participants are welcomed to call the lab technicians/nurses all weekdays during the intervention period if they have any questions regarding their data. All calls to participants are recorded in the participants’ respective journals.

For technical challenges, participants can contact research staff at Steno Diabetes Center by phone via a technical support line.

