#### The usual care group

The usual care group will receive standard of care in accordance with Danish guidelines. In addition, a new Novo Nordisk insulin smart pen is provided to all participants in the usual care group. The smart pen will be used for long-acting insulin for all participants. A second smart pen will be provided to those participants who are also on short-acting insulin. The pens received by the usual care group will be blinded to ensure that participants are unable to see their data. The pens will collect data used for later analysis and comparison of adherence to insulin prescription in the intervention group and the control group. In addition, the usual care group will be provided with a continuous glucose monitor (CGM), which they will be asked to wear the first and last 20±2 days of the trial period. The CGM will also be blinded so that the participants are unable to see their data. The CGM data will be used for analysis of the primary and secondary outcomes. Thus, participants in the usual care group will receive usual care with an addition of the blinded devices. No changes in treatment, including medicine/dosage, will be performed based on the blinded devices, as neither patients nor clinical staff will have access to the data. The control group will not be compensated financially for their participation in the trial. However, by the end of trial, the monitoring lab technicians/nurses will offer to print out the data from the blinded devices and go through them with the participants in the usual care group.

The authors hypothesize that the telemonitoring intervention will significantly improve time-in-range compared to usual care.

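### Baseline for the CGM endpoints and insulin dose is measured in the 2 weeks after randomization, when only the telemonitoring arm is on treatment, so an early effect is partly removed from the primary estimate

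*Protocol article*

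**What the plan says.** The primary endpoint is "Change from baseline in CGM time in range (3.9–10.0 mmol/L) 3 months after randomization" (Primary endpoint). The Statistical analysis section fixes the two windows. Change in TIR, in the other CGM metrics and in insulin dose is the difference between means taken over, in the wording for dose, "total daily insulin dose the 2 weeks before end of trial and the 2 weeks after randomization". The primary model is "An analysis of variance model with the region as a factor and CGM time in range at baseline as a covariate". No CGM period before randomization is described.

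In the telemonitoring arm (The telemonitoring group), training takes place at inclusion, and "The telemonitoring group will use the distributed devices continuously to collect, log, and transfer tissue glucose levels, insulin administration, activity, and sleep at home" throughout, with staff monitoring the data. Scheduled calls are "at 1 week, 1 month, and 2 months after inclusion in the trial", and further calls may be made when staff find them relevant. On their content: "The monitoring lab technicians/nurses may give treatment advice during all calls and potentially change insulin doses based on the monitored data", with a doctor consulted first.

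In the usual care arm (The usual care group), the CGM is worn for the first and last 20 ± 2 days. "The CGM will also be blinded so that the participants are unable to see their data", and no treatment is changed on the basis of the blinded devices.

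**The concern.** A baseline should be something that the allocated treatment cannot have changed. Here the window called baseline opens after allocation. In one arm it contains the start of the intervention: devices in use, staff monitoring and a call that may lead to a dose change. In the other arm it contains only blinded recording. Any TIR gained by the telemonitoring arm in those 2 weeks is credited to its baseline.

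The primary estimate would then be the effect beyond what was already achieved by week 2, not the effect of telemonitoring over 3 months. Time above range, time below range and total daily dose use the same windows. A larger sample does not remove the bias, and a null or small result would be hard to interpret. The limitations in the Discussion do not mention it.

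**Working it through.** **Inputs from the Statistical analysis section:** difference 80 min, SD of the difference 220 min, significance level 0.05 (two-sided, as the formula uses z for α/2), power 0.9, total 320, so 160 per arm at 1:1.

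**The plan's own figure.** n per arm = 2 × 220² / 80² × (1.960 + 1.282)² = 15.125 × 10.51 = 158.9, so 159 per arm and 318 in total, against 320 stated. It reproduces. Power at 160 per arm is Φ(80 / (220 × √(2/160)) − 1.96) = Φ(3.25 − 1.96) = 90%.

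**What the contaminated baseline does.** Let the full effect on final TIR be 80 min, and let a fraction f of it be present in weeks 1–2.

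- Simple change score: 80 − 80f = 80(1 − f).
- Baseline-adjusted model with slope b on baseline: 80 − b × 80f = 80(1 − f·b).

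In the adjusted model it makes no difference whether the outcome is the change or the final value. Subtracting baseline from the outcome changes its slope from b to b − 1 and leaves the treatment coefficient as it was. A simulation of 1,000,000 participants with b = 0.6 and f = 0.25 gave 68.4 min adjusted (formula 68.0) and 60.4 min for the change score (formula 60.0).

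**Assumptions.** The documents give neither f nor b. I take b = 0.7 and f = 0.2, 0.3 and 0.5. If 220 is the SD of change, the two windows have equal variance and b equals their correlation, then:

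- SD of TIR in one window = 220 / √(2 × 0.3) = 284 min.
- Residual SD after adjustment = 284 × √(1 − 0.7²) = 203 min.

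If the planners meant 220 as the residual SD itself, 220 applies instead. Both are shown.

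**Primary model, 160 per arm.** Power = Φ(d / (SD × √(2/160)) − 1.96), with standard error 22.7 at SD 203 and 24.6 at SD 220.

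| f | d = 80(1 − 0.7f) | Power, SD 203 | Power, SD 220 |
|---|---|---|---|
| 0 | 80 min | 94% | 90% |
| 0.2 | 69 min | 86% | 80% |
| 0.3 | 63 min | 80% | 73% |
| 0.5 | 52 min | 63% | 56% |

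**Final TIR without a CGM baseline.** If HbA1c explained none of the variation in TIR, the SD would be 284 and power Φ(80 / (284 × √(2/160)) − 1.96) = Φ(2.52 − 1.96) = 71%. Bringing the residual SD down to 220 needs an HbA1c–TIR correlation of √(1 − (220/284)²) = 0.63 in size.

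**The case against.** The case for the plan has real substance.

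- **Size and direction are not known.** The documents give no early effect. The 1-week call is described mainly as a check that monitoring has started and the devices are understood; data are discussed at 1 and 2 months. That participants can see their own readings is implied by the contrast with the blinded arm, not stated outright. This stands, and it makes the bias conditional: toward no effect if early use raises TIR, as the trial's hypothesis implies, and the other way if early TIR falls. It does not restore the baseline, because advice and dose changes are allowed in every call and monitoring runs from inclusion.
- **Subtracting and adjusting do not harm twice.** A reader might infer that using the same window both as subtrahend and as covariate doubles the loss, or take the change-score powers (74%, 62% and 37% at f = 0.2, 0.3 and 0.5) as those of the primary test. The stated primary model adjusts for baseline, so those figures do not describe it.
- **Validity of the test.** A reader might infer false positives. If telemonitoring has no effect at any time, both windows are unaffected and type I error is not inflated. With an early benefit, a positive result is conservative.
- **Planned power.** The 80 min may have been meant as the contrast the plan defines, with the early part already taken out. The text does not say. In that case the 90% stands, but the endpoint still leaves out whatever happened in the first 2 weeks.
- **Insulin shift.** A reader might count the shift to another basal insulin by trial initiation (Eligibility criteria) as a further source of bias. It applies to participants in both arms, and its falling inside the window is only inferred, so the documents do not support it as a between-arm bias.

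**Conclusion.** The concern holds. The plan fixes a post-randomization baseline that treatment can affect in one arm only, and nothing elsewhere in the article repairs it. The primary model then estimates 80(1 − f·b) min in place of 80, which is 69 to 52 min for f from 0.2 to 0.5 at b = 0.7. Power at 160 per arm is 86% to 63% with residual SD 203, or 80% to 56% with 220. These figures rest on assumed f and b and, for SD 203, on equal variances; they show how sensitive the result is and do not predict it. The fault in the definition does not depend on them.

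Time above range, time below range and total daily dose share the fault. HbA1c does not, provided its blood sample is drawn at the start visit before device use. The harm is a shifted estimate and probably lost power, not an invalid test of no effect.

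**What to change.** Do not use TIR from the first 2 weeks as baseline in the primary analysis. There are two ways.

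**(a) No new data.** Compare mean TIR over the final 2 weeks between arms, adjusted for region and for HbA1c from the start-visit blood sample. Do the same for time above and below range. For total daily dose, adjust for the dose recorded at inclusion. Report the current baseline-adjusted change as supplementary. Cost: the primary endpoint must be reworded, since it is no longer a change from baseline, and the residual SD may rise. Under the assumptions above, power for 80 min lies between 71% (HbA1c uninformative) and 90% (correlation about 0.63). At the lower end this is less than the current model has at f = 0.3 and SD 203 (80%), but more than at f = 0.5 (63%). What it buys is an estimate of the whole effect.

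**(b) Masked baseline before randomization.** Both arms wear the masked CGM and use the masked pen for 2 weeks, and randomization follows. This keeps the change-from-baseline endpoint and the adjusted model, with 94% power at residual SD 203 or 90% at 220. Cost: about 2 more weeks per participant, and it can serve only participants not yet randomized.
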